## Abstract

**Introduction:**

The UK social security system is being transformed by the implementation of Universal Credit (UC), which combines six existing benefits and tax credits into a single payment for low-income households. Despite extensive reports of hardship associated with the introduction of UC, no previous studies have comprehensively evaluated its impact on mental health. Because payments are targeted at low-income households, impacts on mental health will have important consequences for health inequalities.

**Methods and analysis:**

We will conduct a mixed methods study. Work package (WP) 1 will compare health outcomes for new recipients of UC with outcomes for legacy benefit recipients in two large population surveys, using the phased rollout of UC as a natural experiment. We will also analyse the relationship between the proportion of UC claimants in small areas and a composite measure of mental health. WP2 will use data collected by Citizen’s Advice to explore the sociodemographic and health characteristics of people who seek advice when claiming UC and identify features of the claim process that prompt advice-seeking. WP3 will conduct longitudinal in-depth interviews with up to 80 UC claimants in England and Scotland to explore reasons for claiming and experiences of the claim process. Up to 30 staff supporting claimants will also be interviewed. WP4 will use a dynamic microsimulation model to simulate the long-term health impacts of different implementation scenarios. WP5 will undertake cost–consequence analysis of the potential costs and outcomes of introducing UC and cost–benefit analyses of mitigating actions.

**Ethics and dissemination:**

We obtained ethical approval for the primary data gathering from the University of Glasgow, College of Social Sciences Research Ethics Committee, application number 400200244. We will use our networks to actively disseminate findings to UC claimants, the public, practitioners and policy-makers, using a range of methods and formats.

**Trial registration number:**

The study is registered with the Research Registry: researchregistry6697.

Strengths and limitations of this studyImplementation of Universal Credit (UC) is in progress, ruling out a randomised trial, so we exploit the large scale natural experiment generated by phased implementation of the new benefit.We use large-scale population surveys to estimate impacts, but the fixed sample sizes limit the range of subgroup analyses we can undertake.Our mixed methods design enables us to use information about the experiences of people claiming benefit and seeking advice to inform the detailed design of the quantitative analyses.We consulted extensively with UC recipients and organisations representing and providing support for UC recipients in designing the study to ensure that we address questions that matter to UC recipients and organisations that support them.

## Introduction

Social security policies account for up to one-quarter of Gross Domestic Product (GDP) and 40% of public expenditure in high-income countries^1^ and are a key determinant of income and health inequalities.^2^ In the UK, Universal Credit (UC) is transforming social security for working age people by combining six existing benefits and tax credits (known as legacy benefits) into a single monthly payment. UC is designed to improve work incentives for people on low incomes but has been criticised for causing hardship due to the job-seeking requirements and other conditions related to eligibility, and to the way that claims are managed and payments made. UC is being introduced gradually, with rollout due to be complete in 2024.^3^ Research to date has not provided a comprehensive picture of UC’s impact on population health or health inequalities. Our proposed study will be the first to do so, by examining the impact of the introduction of UC on mental health and well-being, and how these effects are moderated by variation in implementation across England, Wales and Scotland.

In preparing our proposal, we updated and extended the literature searches from a recently published study of the impact of UC on psychological distress^4^ by members of our team, to include papers published in 2019–2020. We searched six bibliographic databases (Medline (number of hits=0), PubMed (5), Scopus (5), PsycInfo (0), Social Science Citation Index (8), EconLit (3), using the terms (“universal credit” AND “mental health” OR “wellbeing” OR “well-being” OR depress* OR anxiety OR “psychiatric disorder*” OR “common mental disorder*” OR “psych* morbidity”). We also searched two preprint servers (Socarxiv (2), Medarxiv (1)). We found 17 papers, but no new studies, other than our own,^2^ that dealt with the health impacts of UC.

Several reports from public bodies draw attention to possible health harms. Based on evidence from local authorities and charities, the UK Parliament’s Public Accounts Committee has raised concerns about financial hardship associated with the 5-week wait for the first payment, compounded by delays in processing new claims.^5^ The UN Special Rapporteur on extreme poverty and human rights highlighted difficulties faced by ‘poorer and more vulnerable households’ in negotiating the online application process, concluding that ‘UC was harming many claimants’ mental health, finances, and work prospects’.^6^ Doctors’ organisations have reported increased consultations in general practices following the transition to UC.^7^ Significant concerns have been raised about the impact of UC on rising child poverty in the UK.^8^ Qualitative studies have reported ‘widespread and deeply negative impacts on wellbeing’.^9^ In our own research,^10 11^ claimants reported that the threat of sanctions, delays in payment and financial insecurity associated with UC harmed their physical and mental health. There has been one quantitative study of health impacts to date, again by members of our team.^4^ This study compared changes in mental health among unemployed people in areas where UC had been implemented with areas where legacy benefits remained in place, finding a seven-percentage point increase in psychological distress in the former.

Although existing evidence suggests mainly adverse effects, UC may improve health if it provides a higher or more dependable income for recipients than existing benefits, or if it supports paid work. Research conducted by the Department for Work and Pensions’ (DWP) found that more intensive support for job-seeking under UC increased earnings^12^ and helped unemployed claimants return to work sooner.^13^

To date, the evidence of health impacts relates to a period when UC had only been implemented for some groups of new claimants. The overall health and equity impacts may change markedly as legacy benefit recipients migrate to UC. Substantial but temporary changes in the way UC is administered were made in response to the economic shock associated with the COVID-19 lockdown measures in early 2020. Conditionality and some forms of debt recovery were suspended for 3 months and have since remained well below prepandemic levels. The standard cash allowance (the most a household could receive, before taking income and savings into account) was raised by £1000 per annum from April 2020 until October 2021^14^ A very large number of new claims were made and processed in the early months of the lockdown. Claims rose 9-fold, to 500 000 per week in early April 2020, and the caseload doubled from 3 to 6 million, before new claims returned to previous levels by July 2020.^15^ A new cohort of UC recipients has been created whose composition is likely to differ significantly from the pre-COVID-19 caseload (eg, they are less likely to have received benefits in the past and more likely to have savings).^16^ As well as estimating the impact of UC on population mental health, we shall explore the experiences of these new recipients to gain insights into whether differences in health impacts might be expected.

Our objectives are: (1) to measure the impacts on mental health and well-being among adults and children affected by UC, compared with a legacy-benefits comparator group; to explore how impacts are distributed and effects vary between England/Wales and Scotland, and the implications of the COVID-19-related changes to UC for the health of recipients; (2) to identify features of the UC claim and payments process associated with health difficulties for claimants, and to explore inequalities within and between regions in the pattern of advice-seeking from Citizens Advice (CA); (3) to explore the ways in which the experience of claiming and managing UC affects claimants’ health, and how experiences differ between England/Wales and Scotland; (4) to develop a microsimulation model to investigate possible income, employment and health consequences of differing UC implementation scenarios, up to 10 years post implementation; (5) to measure the cost–consequence of UC, analyse its distributional consequences and conduct cost–benefit analyses of moderating/mitigating measures implemented in Scotland or by specific local authorities.

## Methods and analysis

### Study design

We will undertake a mixed methods study with five closely linked work packages (WPs). WP1 will take a natural experimental approach to identify the effects of UC on mental health and well-being using two large-scale population surveys, the UK Household Longitudinal Study (UKHLS)^17^ and the Annual Population Survey (APS).^18^ We shall use the information about the phased implementation of UC that is made publicly available via the DWP’s Stat-Xplore system^19^ to define exposed and unexposed groups and compare changes in the health of survey respondents exposed to UC, with changes in the health of respondents living in areas where legacy benefits still apply. We will also use a longitudinal neighbourhood dataset for 42 000 small areas (Lower Layer Super Output (LSOA) areas in England and Wales; Datazones in Scotland), the National Institute for Health Research (NIHR) North West Coast Applied Research Collaboration—Place-based Longitudinal Data Resource.^20^ The dataset includes monthly measures indicating which population groups (eg, new claimants, existing claimants, people with/ without children, people with disabilities) were affected by the phased rollout of UC in each neighbourhood in each time period. To identify any area-level mental health effects of UC, we will use a composite neighbourhood mental health measure—the Small Area Mental Health Index (SAMHI), available annually for the same small areas, but adapted to include Scotland.^21^ Using the COVID-19 waves of the UKHLS, we shall compare mental health among new UC claimants, other respondents who have experienced income losses and existing UC claimants. These analyses will be primarily descriptive rather than designed to formally identify impacts.

WP2 will analyse administrative data collected by CA on the characteristics of people seeking help in connection with UC claims between 2017 and 2020, a survey conducted in the North East of England on financial stress associated with the UC application process in September/October 2019, and a linked dataset derived from the Liverpool ‘advice on prescription’ service, which combines CA data on advice-seeking with information about use of health and social care services.

WP3 comprises two qualitative studies: (1) a longitudinal qualitative and photovoice^22^ study of UC claimants and (2) qualitative interviews with DWP JobCentre Plus staff who support claimants through the process of claiming and front line staff from education, local government, housing and the voluntary and community sectors who support people claiming UC. We will seek to interview claimants at two timepoints, 18–24 months apart, to explore how the experience of claiming and receiving UC is influenced by other changes in life circumstances, such as transitions into or out of work, changes in relationship status, birth of children or changes in housing arrangements. Use of photovoice methods, alongside more conventional qualitative methods, will enable the follow-up interviews to be participant-led.

WP4 will develop a stochastic dynamic microsimulation model of the longer term health impacts of UC, building on an existing static microsimulation model of income and welfare policy (UKMOD, www.microsimulation.ac.uk/ukmod), and incorporating information about effects and mediators from the other project WPs. We shall use the model to simulate the possible health impacts of different UC implementation scenarios, and to explore how these differ between subgroups of the working age population, defined by personal characteristics, household type or geography.

WP5 will undertake a cost–consequence analysis of UC and assess its distributional impacts by health, income and other individual and area-level characteristics. We will identify and estimate the magnitude of the wide range of potential positive and negative consequences of introducing UC. We will provide, where appropriate, monetarised valuations of these effects and detail which sectors and government departments experience them. Costs and consequences associated with implementing UC will be compared with a baseline scenario of continued legacy benefits. We will also undertake cost–benefit analyses of a range of actions that have been implemented in Scotland or locally within England to mitigate possible negative impacts of implementing UC.

### Intervention

UC combines six existing benefits and tax credits for people who are unemployed or on a low income into a single monthly payment. It is intended to encourage an early return to work by incorporating support for job-seeking and removing disincentives associated with high marginal withdrawal rates under the legacy benefits. The differences between UC and the legacy benefits are summarised in figure 1.

**Figure 1 F1:**
[figure not shown]
Universal Credit and legacy benefits (source: reference^2^). ESA, Employment and Support Allowance; JSA, Job Seeker's Allowance.

UC began to be used for new claims in October 2013, with rollout for new unemployed claimants complete by December 2018. Existing claims for legacy benefits and tax credits will be transferred to UC in a process of ‘managed migration’. The process began with a geographically limited pilot which was suspended early in 2020, but is expected to recommence in 2022, although how migration will now be managed is not yet known.

UC may improve recipients’ health via increased income and employment, but some features of its design and delivery may be harmful. The application of conditionality and sanctions, the minimum 5-week wait for the first payment, which may in practice be much longer,^3^ the two child limit and benefit cap, and the inclusion of support for housing costs within a single monthly household-level payment made to one individual, have all attracted concern. Some households, such as working families living in rented accommodation, will have higher incomes from UC than they would receive from legacy benefits, but others, including people receiving disability benefits, self-employed people with low earnings, and some working lone parents who were formerly receiving tax credits, may lose income.^23^ UC is a UK-wide system but in Scotland, under arrangements known as ‘Scottish Choices’, claimants can opt for 2 weekly payments, or to have the housing element paid direct to their landlord.^24 25^

The effects on health of the transition to UC are therefore likely be complex and geographically variable, with some households benefitting from improved living standards and greater financial security, but others facing an increase in hardship, insecurity and debt.^26^ Effects may be direct, for example by increasing stress, or be mediated by changes in behaviours such as smoking, drinking or criminal activity.^27^ Children’s health likewise will be affected directly by changes in household living standards,^28^ for example, in relation to diet or warmth, but also by effects operating through parental stress and consequent changes in parenting and other behaviours.^29^

As noted above, substantial but temporary changes in the way UC is administered have been made in response to the economic shock associated with the COVID-19 lockdown measures. As well as estimating the overall impact on UC on population mental health, we shall explore the experiences of these new UC recipients to gain insights into whether differences in health impacts might be expected.

### Sample selection

In WP1 we will analyse data on people of working age and their children from 2009 to 2022 in the UKHLS, and on people of working age from 2011 to 2024 in the APS. The UKHLS and APS use stratified clustered random probability samples of the UK population. The CA surveys (WP2) include adults in England who have contacted CA for assistance with claiming UC from 2017 onwards. For a subsample of respondents from North East England, a survey conducted by CA was in August 2019 and a follow-up questionnaire was administered in October 2019 to all individuals who had made a UC claim to understand the characteristics of people who experience financial hardship. The ‘advice on prescription service’ data is available for people engaging with CA Liverpool from 2014, but linked data will span 2010 to 2023.

The samples of UC claimants for WP3 will be drawn from two large urban areas, Tyne and Wear (population 1.1 million) in North East England and the Glasgow City Region (population 1.2 million) in Scotland. A number of recruitment strategies will be used, including via gatekeepers^8 9^ in public, voluntary and community sector organisations, workplaces and trades unions, and via social media and leaflets placed in community locations such as libraries. We will aim for a maximum variation sample, taking account of age, gender, ethnicity, household composition, education level, health, disability, employment and housing status. The sample will include people who have been on UC for some time, new claimants and those transferring to UC from legacy benefits. We will include people who were claiming UC prior to March 2020, people who claimed UC during the UK’s lockdown period and those who have become claimants later due to the economic impact of the pandemic. We will recruit staff from a range of organisations in each locality via our extensive professional networks in each conurbation.

### Sample size and statistical power

The UKHLS includes approximately 40 000 households who are surveyed annually. The 2009–2022 survey datasets will include approximately 280 000 observations on around 52 000 adults and 30 000 observations on 5000 children. To identify the impact of UC, we will conduct difference-in-difference (DiD) analyses, comparing members of households newly exposed to UC as rollout proceeds, with households who are unlikely to be exposed. Focusing on child health outcomes, because the numbers available are smaller, in the UKHLS datasets from 2009 to 2018 we will have 300 children in the intervention group and 3300 in the control group, providing 80% power to detect an 8% relative increase in Strengths and Difficulties Questionnaire (SDQ) scores. This is a markedly smaller effect than the 20% relative increase in the prevalence of psychological distress we found in our previous study^4^ of the impact of UC on adult mental health up until 2018, so provides a conservative estimate of the power of the proposed study. The sample size in the UKHLS COVID-19 surveys is approximately 10 000, of whom approximately 4000 reported substantial (>5%) income losses, and around 300 reported new UC claims in the April survey wave. Currently, nine waves of data are available, from April 2020 to September 2021, with questions about UC included in waves 1, 2, 4, 6, 8 and 9.^30^

The APS collects self-assessed health and well-being data on approximately 180 000 working age people per year, so provides good power for England–Scotland comparisons and other subgroup analyses. Our analysis of area level mental health effects will use annual data from a longitudinal dataset of 42 000 neighbourhoods from 2011 to 2022, or approximately 504 000 neighbourhood-years.

The CA survey dataset contains information on approximately 280 000 people who seek advice. The longitudinal survey contains information on 250 people, with a response rate of 85%. The advice on prescription dataset contains information on approximately 5000 people each year since 2014.

For the qualitative study, we will recruit up to 80 UC claimants aged 18–66 (state pension age), divided equally between the 2 study sites. We will seek to reinterview 40 first round respondents 18–24 months after their first interview, a subsample of interviewees using photovoice methods.^22^ We will aim to interview up to 15 staff from a range of organisations in each study site.

WP4 and 5 draw on data from WP1–3 above and from the additional sources listed in the analysis plan below.

### Outcomes

Our primary focus is on mental health and well-being. Mental health is an important dimension of overall health and well-being, that is sensitive to the effects of changes in employment or income,^31 32^ and an important determinant of physical health. Parental mental health is also an important mediator of the impact of poverty on child health.^33^ In the survey analyses (WP1), we shall use standard measures of mental health and well-being, such as the Mental Component Summary of the 12-item Short-Form Health Survey (SF-12) for adults, the SDQ for children,^34^ and the Office for National Statistics (ONS) ONS4 measure of well-being (life satisfaction, sense that life is worthwhile, happiness and anxiety).^35^ Secondary outcomes include other mental and physical health measures available in the surveys. In the neighbourhood-level analyses, we will use a composite mental health measure, the SAMHI.^21^ In the CA surveys in WP2, we shall use presence of a self-reported long-term mental health condition. WP4 and WP5 will use similar outcomes to WP1, and WP5 will also explore the costs and non-health consequences of implementing UC. In WP3, we shall explore other health outcomes identified as important by respondents.

### Analysis plan

To identify the effects of UC in the UKHLS and APS datasets (WP1), we will fit difference-in-differences (DiD) models, with terms for group and period to define respondents who are exposed or unexposed to UC, depending on their sociodemographic characteristics, location and date of interview, and a group by period interaction term to identify the effect of UC. We will add individual and area-level covariates to account for time-varying confounders^36^ and fit mixed-models to account for clustering of observations within households and areas. Sensitivity analyses will be conducted using alternative definitions of exposed and unexposed populations. We will test the validity of the key identifying assumptions, such as common preintervention trends, and use additional (eg, matching) methods if needed. We will also conduct falsification tests using placebo outcomes to test for specificity of effects.

For the SAMHI analyses, we will use fixed-effect panel regression methods to investigate whether increases in UC in each LSOA are associated with changes in mental health problems, while controlling for time-varying confounders (eg, local government expenditure).^37^ We will check the robustness of the results by using alternative ways of estimating effects, such as continuous DiD and synthetic control methods^38^ to compare outcomes in areas where UC has been introduced and areas not yet exposed.

To investigate the extent to which changes in income, employment status and financial housing difficulties (such as rent arears) mediate the effects of the introduction of UC on health outcomes, we will undertake causal mediation analysis adjusting for time-varying confounding.^39–41^ Subgroup analysis will investigate differences in health impacts between Scotland and the rest of Great Britain (GB), or between areas with differing labour market characteristics. By stratifying the analysis before, during and after the pandemic we will investigate whether moving onto UC had the same effect during these different time periods, when the policy and wider social context were very different. Using the COVID-19 waves of the UKHLS, we shall compare mental well-being among new UC claimants, other respondents who have experienced income losses and existing UC claimants. These analyses will be primarily descriptive rather than designed to formally identify impacts.

In WP2, we will carry out descriptive analyses of the England-wide CA survey data to summarise the health and sociodemographic characteristics of people seeking advice in applying for UC, and explore differences at the local authority level in key demographic and health characteristics of advice seekers. We will use the longitudinal CA dataset to describe the sociodemographic and health characteristics of people who are most and least likely to experience financial insecurity as a result of the 5-week wait for the first payment. We will also apply longitudinal multivariable regression to the advice on prescription linked dataset, similar to the methods used in WP1. We will use the cross-sectional national data from March 2020 onwards to explore changes in the sociodemographic and health profile of people seeking advice with UC claims following the COVID-19 pandemic.

In WP3, we will apply thematic content analysis to the longitudinal qualitative data,^42^ using NVivo software to assist data management, retrieval and sharing between members of the research team. A comparative analysis across time, locality and participant characteristics will be undertaken to identify possible pathways linking the experience of claiming UC with health outcomes, and how they vary between claimants and between study sites. This will enable identification of differences of experience by locality and in-depth analysis of characteristics including gender, age and employment status, as well as facilitating comparisons of the experiences of longer term (pre-COVID) and post-COVID claimants. Photovoice data will be coded and incorporated within the analysis of the interview material.^22^ Interviews with staff will also be analysed thematically.

In WP4, we will first create a dynamic, synthetic population that reflects the GB population, using data from UKHLS, APS, census data, population projections, mortality estimates and the Family Resources Survey. We will develop a new stochastic dynamic microsimulation model based on the existing UKMOD income and welfare policy model,^43^ coupled with estimates of the relationship between UC, income, employment and health. We will use the model to simulate the effects on health of different UC implementation scenarios compared with three baseline scenarios: the continuation of legacy benefits; UC as it existed in the early months of the COVID-19 pandemic; and UC in its contemporary form (ie, at the time of running the model). Implementation scenarios will include varying levels of standard allowance, conditionality, payment frequency and so on. Under each scenario, we will transition the synthetic population forward in 1 year increments for up to 10 years, so that we can compare the effects on health and health inequalities of the different policy choices. We will check the robustness of the model by comparing simulated health outcomes with known outcomes from UKHLS waves that were not used to parameterise the model and from other surveys such as the Scottish Health Survey. To allow for the uncertainty in the sample-based parameter estimates used to build the model, we will use Monte Carlo simulation (10 000 runs) to derive 95% credible intervals.

WP5 comprises three linked analyses: ex post cost–consequence and distributional cost–consequence analyses of the implementation of UC, and an ex ante cost benefit analysis of measures to mitigate against possible adverse effects of UC. We will follow HM Treasury Green Book^44^ guidelines for economic evaluation, to enable comparability with other evaluations of UK Government policies. We will obtain measures of costs of implementing legacy benefits, UC and mitigating measures through liaison with project partners. We will consider a wide range of consequences, informed by liaison with stakeholders and the findings of WPs 1–3. They will include, but not be limited to, health and well-being; income (at both individual and household level); employment; economic productivity (gross value added); and use of health and care services. We will use estimates of the short-term effects of UC from WP1, supplemented by additional analyses using similar methods as far as possible, but considering alternatives (eg, lagged dependent variables, synthetic controls) where DiD assumptions are not met.^45 46^ Economic, health and well-being outcomes will be monetarised where appropriate using standard methods.^47 48^ The initial time horizon for the accrual of costs and consequences will be 10 years (consistent with WP4), though we will consider alternative time-horizons informed by discussions with stakeholders.

The overall duration of the study is 52 months from May 2021–August 2025. Primary data gathering began in January 2022 and will be completed in September 2024.

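### One group-by-period interaction is planned for a staggered rollout with two different comparators; under the area comparator the UC effect can be badly biased if it varies with time since rollout

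*Protocol article*

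**What the plan says.** All references are to the Protocol article.

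- **Estimator (Analysis plan).** The survey models are difference-in-differences with terms for group and period "and a group by period interaction term to identify the effect of UC". Respondents are classed as exposed or unexposed "depending on their sociodemographic characteristics, location and date of interview". Covariates are added, and mixed models handle clustering.
- **Rollout (Intervention, text after Figure 1).** "UC began to be used for new claims in October 2013, with rollout for new unemployed claimants complete by December 2018". Existing legacy claims were still awaiting managed migration.
- **Data windows (Sample selection).** UKHLS 2009 to 2022, APS 2011 to 2024: four and six years beyond December 2018.
- **Comparator, first description (Study design).** Changes in exposed respondents are compared "with changes in the health of respondents living in areas where legacy benefits still apply".
- **Comparator, second description (Sample size and statistical power).** The analysis is described as "comparing members of households newly exposed to UC as rollout proceeds, with households who are unlikely to be exposed". For child outcomes in 2009 to 2018 the groups are 300 and 3300.
- **Constancy of the effect (Introduction).** "The overall health and equity impacts may change markedly as legacy benefit recipients migrate to UC".
- **Survey safeguards (Analysis plan).** Alternative exposure definitions, placebo outcomes, strata by pandemic period, and: "We will test the validity of the key identifying assumptions, such as common preintervention trends, and use additional (eg, matching) methods if needed".

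**The concern.** When areas adopt a policy at different dates, a single exposure coefficient from a model with area and time effects averages many two-group, two-period contrasts. In some of these the control is an area that adopted earlier. If its effect is still changing, that change is subtracted from the later adopter's effect. The coefficient equals the average effect when the effect is constant; otherwise it can miss in either direction.

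Whether this bites depends on the comparator, which the plan leaves open. The area comparator runs out after December 2018 for new unemployed claimants, yet several later years of data are included. None of the listed survey safeguards deals with effects that vary with time since rollout: pre-trend tests look before exposure, and the pandemic strata split by calendar period. The estimate also travels, since WP5 takes short-term effects from WP1 and WP4 draws on effects from the other work packages.

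**Working it through.** **The plan's own figures.** The plan states no figure for this bias. The power statement supplies one usable input, the control share: 3300 / (300 + 3300) = 0.917. Treating those controls as never exposed is an assumption.

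**Assumptions (the plan gives neither cohort shares nor effect shapes).** Five equal annual cohorts, 2014 to 2018; no noise; parallel trends; k = years since rollout. The model has area effects, year effects and one exposure term. The target is the average effect over exposed observations.

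**Mechanism in one contrast.** Take an area exposed in 2014, one exposed in 2018, and the change from 2017 to 2018.
- Effect k + 1: the late area moves 0 to 1 and the early area 4 to 5. The contrast is 1 − 1 = 0, against a true effect of 1.
- Effect fading as 1 − k/4: the late area moves 0 to 1 and the early area 0.25 to 0. The contrast is 1 + 0.25 = 1.25, against a true effect of 1.

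**True averages, effect k + 1.** 2009–2018: cohorts have 5, 4, 3, 2 and 1 exposed years, so (15 + 10 + 6 + 3 + 1) / 15 = 35/15 = 2.33. 2009–2022: 9, 8, 7, 6 and 5 years, so (45 + 36 + 28 + 21 + 15) / 35 = 145/35 = 4.14.

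**Results** (percentages from unrounded values):

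| Effect | Window | True average | Coefficient, all areas eventually exposed | Bias | Bias at 0.917 never exposed |
|---|---|---|---|---|---|
| constant 1 | both | 1.00 | 1.00 | 0% | 0% |
| k + 1 | 2009–2018 | 2.33 | 1.17 | −50% | −6.5% |
| k + 1 | 2009–2022 | 4.14 | 0.50 | −88% | −4.9% |
| min(k + 1, 3) | 2009–2018 | 2.07 | 1.33 | −35% | −4.6% |
| min(k + 1, 3) | 2009–2022 | 2.57 | 1.42 | −45% | −1.5% |
| max(1 − k/4, 0) | 2009–2018 | 0.67 | 0.96 | +44% | +5.7% |
| max(1 − k/4, 0) | 2009–2022 | 0.36 | 0.99 | +177% | +7.3% |

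**Other assumptions.** Six cohorts (2013 to 2018, equal or back-loaded), growth 0.25 + 0.25k and fading 0.7^k gave −42% to −92% and +24% to +128% with no never-exposed group. At the 0.917 share they gave −5% to −9% and +4% to +7%.

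**Household comparator.** Now fit a common group term, an area-specific before/after term and one interaction, with never-exposed households in the same areas. The group gap is c before rollout and c plus the effect afterwards, so with equal group shares the interaction is the mean gap after minus the mean gap before. For k + 1 in 2009–2018 that is 35/15 = 2.33: no bias. It was nil for every shape and window run. If the group gap may differ by area, areas are weighted by years before × years after: 25, 24, 21, 16 and 9 (sum 95). Their mean effects are 3, 2.5, 2, 1.5 and 1, so the estimate is 210/95 = 2.21 against 2.33, or −5%, with all weights positive.

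**What the nil result rests on.** If the two household groups may follow different calendar-time paths (group-by-year effects, with area-by-group and area-by-year effects), the area-only answers return for 2009–2022: 0.50 v 4.14 for growth and 0.99 v 0.36 for fading.

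**The case against.** The strongest reply is that every comparator the article names is unexposed, exposure is defined by person type and date as well as place, and no two-way fixed-effects model is specified for the surveys. The power statement implies a control group of about 92%, at which the error is under 10% in the 2009–2018 and 2009–2022 calculations. By 2018 rollout was complete only for new unemployed claimants, so legacy recipients remained available for comparison. The article condenses a fuller plan that may settle the matter.

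Most of this stands, and it limits the point. A reader might infer that the plan uses already-exposed areas as controls, or that the estimate is biased whenever the effect changes with time since rollout. The text says neither, and the household comparator can recover the average effect. What remains is a stated single-coefficient estimator and two comparators, one of which fails after 2018 for the group whose rollout was complete.

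Three further inferences are not supported:
- The pre-trend sentence does not say that the reported estimator will be switched after a test; it speaks of additional methods.
- The neighbourhood analysis, where "we will use fixed-effect panel regression methods to investigate whether increases in UC in each LSOA are associated with changes in mental health problems", has continuous exposure, so these calculations do not carry over. It already lists robustness checks against areas not yet exposed.
- The Introduction's remark about changing impacts concerns legacy recipients migrating to UC. It shows that constancy cannot be assumed, but not that effects grow or fade with years since area rollout.

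On WP5, the article does allow alternatives where the difference-in-differences assumptions fail, which softens the downstream risk.

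**Conclusion.** The concern holds conditionally. The survey analyses rest on one group-by-period interaction under staggered rollout, and the comparator that identifies the effect is not fixed. If areas still on legacy benefits are the comparator, pooled with area and time effects, the coefficient can be badly wrong when the effect varies with time since rollout: −35% to −88% for growing effects and +44% to +177% for fading ones in the 2009–2018 and 2009–2022 windows. These sizes are illustrations under assumed equal cohorts and effect shapes, with no never-exposed group; they are not estimates of the bias in this study. With households unlikely to be exposed as the comparator, the error is about 1% to 9% at a 92% control share in a two-way model, or nil for the interaction with a common group term. Both results require common trends between the two kinds of household, including through the pandemic. The 92% comes from the child sample for 2009 to 2018 and need not hold for adults or the APS. A constant effect gives no bias under any reading.

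**What to change.** For the UKHLS and APS analyses:

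1. Reconcile the two comparator descriptions and state which one identifies the effect, with an explicit rule for data after December 2018.
2. Make the primary estimate a staggered-adoption difference-in-differences (group-time average effects, stacked, or imputation), with only not-yet- or never-exposed respondents as controls.
3. Pre-specify how the group-time effects are aggregated into one average effect, and show the event-time estimates beside it.
4. Keep the single-interaction model as a sensitivity analysis.

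The data are unchanged. The cost is revised analysis wording, some extra coding and somewhat wider intervals. If the full analysis plan already fixes the comparator and estimator in this way, a sentence in the article saying so is enough.
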